### Study population, recruitment, and retention

Women were eligible to participate in the study if they were between the ages of 18-44 years, currently in a heterosexual relationship with a male partner, responded in affirmative to past year sexual or physical IPV, and was not pregnant or pregnant in their first trimester. Study exclusion criteria included cognitive impairment (e.g. slurred speech), seeking treatment for life threatening emergency care, and intending to relocate within two years. Research assistants approached women in the waiting rooms of participating clinics, verified eligibility for the study, and asked women to take an assessment screening that contained items from an abuse assessment screen that is widely used by International Planned Parenthood Federation/Western Hemisphere Region (IPPF/WHR) in Latin American and Caribbean countries and has been previously used in studies occurring in Mexico City
[38–40]. Based on feedback from piloting the assessment, the final tool consisted of eleven questions in order to build rapport between the research assistant and participant. The first nine questions were in regards to the woman’s health and relationship with her partner, including emotional abuse, as directly asking about physical or sexual IPV at the very beginning of the assessment was rendered as too sensitive during our piloting phase. Based on feedback from focus groups carried out with IPV survivors at a community domestic violence agency, concrete examples of physical and sexual IPV were included in the questions (see Figure 
1). If a woman answered at least one affirmative response to the validated screening items on physical and sexual IPV contained in the assessment, they were invited to participate in the study; those interested completed written and/or verbal informed consent. Both the assessment and the informed consent process took place within a private area of the clinic.

**Figure 1 Fig1:**
[figure not shown]
**Abuse assessment screening.**

At baseline data collection, women were asked for their contact information, including the names of three other people in case the woman could not be reached for follow-up appointments. Research assistants called every number provided by the participant to verify that the phone numbers were functional. Participants received a call on average 3 days after they completed the baseline to verify contact information. All participants agreed that it was okay to call them and research assistants were trained to ask if it was a safe time to talk and did not mention violence or the study if another person answered the phone.

All women received monthly follow-up phone calls to remind them of 3 month and 15 month follow-up appointments. At all times their disclosure of IPV remained confidential and the purpose of the study was not be shared with anyone. Upon conclusion of the surveys and counseling at baseline, all women received a snack for their time. At the three month follow-up they received a gift card for $15 USD and at the fifteen month follow-up participants will receive $20 USD. The amounts and type of compensation were determined based on consultation with Mexfam (Mexican Foundation for Family Planning) and the MoH, as well as responses from a short survey given to women at health clinics during our piloting phase regarding their preferred mode of compensation (e.g. phone credit, food, gift card, *etc*).

Data were collected through a computer-assisted survey which has been shown to improve response rates to sensitive behaviors
[41]. Participants completed the survey in a private space in the clinic and were able to listen to the questions in Spanish through headphones and answer on the keyboard. Research assistants were available during this period in case the participant had any questions. Given that clinics were randomized and not individuals, research assistants were not blinded to whether they were in a treatment or control clinic.

### Intervention description

Women who participated in the study at treatment clinics received the following intervention: (1) integrated IPV and health screening; (2) supportive care; (3) safety planning and harm reduction counseling; (4) supportive referrals; and (5) booster counseling sessions at three months post baseline. The majority of materials utilized for the intervention were adapted from existing IPPF/WHR materials used in other Latin American and Caribbean contexts and were adapted to the characteristics of Mexico City
[38]. A referral directory was also created with the contact information of local community agencies that provide services to IPV victims. During the development phase of the referral directory, IPV staff at the MoH suggested that only community agencies providing free services be included. All community agencies listed in the directory were visited by research staff and addresses and phone numbers were verified. Furthermore, for each community agency, research staff obtained the name of a specific contact person to include in the referral directory. Contact names were included in the referral directory based on pilot focus group research with IPV survivors enrolled at a community agency. Pilot work revealed that women felt more comfortable asking for services if there was a specific person to contact at an agency; and that only having the name of an agency was a deterrent.

Of the agencies, two programs were highlighted: (1) SEPAVIGE, the MoH IPV program, (Gender based Violence Special Services) and UAVIF (Family Violence Prevention and Care Unit). There are approximately 14 SEPAVIGE units located primarily within hospitals. Key services include free psychological treatment and group therapy to IPV victims. UAVIF is associated with the Ministry of Social Development and it consists of 16 units in each district of Mexico City. Each unit offers legal and psychological services. They are also in charge of identifying women eligible for an IPV conditional cash transfer program. The referral directory was handed out to nurses during the training Details are presented in Table 
1.

**Table 1 Tab1:** **Intervention components**

Intervention component	Description
Integrated IPV and health screening	Women will be screened for IPV including emotional, physical, and sexual violence, as part of a general health assesment.
Supportive care	Nurses will be trained to provide non-judgmental and empathetic counseling, .
Safety planning and harm reduction counseling	Nurses will discuss safety planning measures with women, including escape routes or places of refuge, packing and storing a bag with important belongings, memorizing phone numbers, talking to children about what to do in cases of violence, and staying away from rooms with weapons. Harm reduction counseling will include the partners’ use of alcohol and illicit drugs, how to remove weapons, options for protecting reproductive health, such as protecting against unplanned pregnancy, sexually transmitted infections, and other individual-specific health risks.
Supportive referrals	Women will be counseled about local IPV and sexual assault resources according to their specific needs. Access and utilization will be facilitated by contacting programs together or by offering the woman step-by-step directions. Business-sized referral cards which contain contact information for local resources, will be given to all women.
Booster counseling sessions at 3 months	Components of above screening, referral, safety planning and harm reduction will be reviewed and redelivered to program participants. Sessions will occur in clinic and information will be recorded in patient charts.

Nurses from all 42 health clinics were invited to participate in the training based on the following criteria: morning shift nurses (due to the walk-in basis of appointments and afternoon shifts not occurring at all clinics) and not a field nurse (due to their limited time at the health clinics). A total of 197 nurses (approximately 8% male nurses and 45% in treatment clinics) received the training. 147 nurses are actively participating in the study (49% in treatment clinics) (26% staff dropped out primarily due to staff turnover at clinics). On average, 4 nurses were trained at each health clinic. Nurses in the intervention group received a 3 day training that covered all the topics of the intervention and then nurses received up to 3 visits by research staff to practice delivering the intervention through role – playing exercises individually and in the clinics. In-depth training was needed as nurses did not feel very comfortable talking about IPV and several rounds of role playing exercises were needed for nurses to gain confidence. Role-playing exercises with research staff were chosen as it preserved rapport between nurses and the research team as well as increased confidentiality of nurses requiring additional training. All training activities were conducted by the research team, IPPF training consultants, and invited guests from local organizations and government offices who specialize in this area. Specific topics in the training included an introduction to IPV, health consequences of IPV, legal considerations in Mexico City, methods to screen for violence and assess for health implications such as reproductive coercion, safety and ethical considerations, referral methods and linkages to other organizations in the community. An educational video modeling the counseling sessions was also developed by the study team for the training of treatment nurses. This video was shown and discussed during research assistant visits to the health clinics as part of the training.

Women in the control clinics were given a referral card containing general information on IPV and a list of resources, which was consistent with the current goal for standard of care in the Mexico City MoH. The referral card is the size of a business-card so that it may easily be hidden from male partners, and is widely used in other IPV screening programs
[42]. Staff in control clinics received a one day training that focused mainly on sensitizing nurses and training them on using the abuse assessment. Control clinic staff will receive the intervention training upon completion of the study.

### Ethics

Conducting research with women who have recently experienced violence represents a number of safety concerns
[43]. Ethical procedures were guided by World Health Organization standards for conducting research on domestic violence
[44] and were taken into account during study preparations. First, all women will provide informed consent which stresses the voluntary nature of the study, the ability to skip questions as necessary, confidentiality, and outlines potential risks and benefits of participation. At the end of the survey, health care providers explain available resources for emotional support and provide a list of resources. Second, the study was designed so as not to reveal to the partner the purpose of the study or the woman’s participation in the study. At all times a woman’s disclosure of IPV remained confidential, including the three friends or family members she listed in case she could not be contacted at follow-up. During follow-up calls, the specific purpose of the study was not given; rather, it was referred to as a study on “women’s health and families”. All research staff were trained by senior study personnel on study ethics. Regular de-briefings, including recommendations for self-care, occurred with research assistants to reduce vicarious trauma among staff. Research staff and nurses participating in the study were encouraged to report any emotional distress, including if they were struggling with experiences of victimization in their own lives, to principal investigators. Study procedures have been approved by the Yale School of Public Health (Protocol # 1202009793), Innovations for Poverty Action (Protocol # 555.23May-001), and National Institute of Public Health (Mexico) (Project #1089) institutional review boards.

### Quantitative assessments & analytic plan

Our primary outcome is past-year IPV
[32] and our secondary outcomes include past-year reproductive coercion
[7, 23], use of community-based resources
[33], safety planning measures
[33], and quality of life
[34]. Descriptive statistics will be used to assess achievement of Aim 1. For the remaining aims, the follow analyses plans will be undertaken: (1) assess if randomization of health clinics was successful by examining if there are statistically significant differences between women’s demographics, by treatment arm, through chi-square or t-tests; (2) assess for differential loss to follow up by demographics and baseline IPV severity; (3) assess if IPV and secondary outcomes (reproductive coercion, safety planning, use of community resources, quality of life) differed at baseline, by treatment arm; and (4) conduct multilevel analyses of the effect of the intervention on outcomes utilizing appropriate models that will account for potential clustering for repeat measures, time, and at the clinic level. We will subsequently estimate adjusted models if any demographics significantly varied at baseline. Analyses will first be undertaken using the intent-to-treat approach. Following this, a per protocol analysis will be undertaken to determine whether effectiveness varied by adherence (i.e. attending the three month booster counseling session) and potentially nurse adherence.

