### Randomization, sample size, and power analysis

Approximately 900 women from 42 health clinics were calculated to be sufficient sample size in order to achieve 80% power to detect a 15% difference in IPV frequency between treatment versus control arms at the α < 0.05 statistical significance level. A conservative intraclass correlation of 0.07 was assumed for clustering at the clinic level. This total sample size takes into account an attrition rate of 45%. The study proposal has budgeted for tracking participants that are relatively more difficult to track in order to reduce attrition.

Health clinics were first stratified by city zone (e.g. Center, North, East, West, South). Of the 57 health clinics that met inclusion criteria, 42 were randomly selected and randomized to treatment or control conditions, based on sample size calculations. To select the 42 health centers, all centers were assigned random numbers in Excel and sorted from smallest to largest; health centers were selected based on city zone and in order of their random number. Randomization was completed in STATA.

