## Discussion

This study seeks to train and improve nurses’ capacities to deliver an intervention for women currently experiencing IPV that present at health clinics in Mexico City. If found efficacious, this study may have an important influence on programming and policy for the health sector responses in city-based clinics serving low-income women in the region. Findings may also contribute to the evidence-base for comprehensive prevention strategies to reduce IPV and to respond to the needs of survivors. This intervention may be an effective health-sector tool to reduce IPV and mitigate negative effects, in addition to many other approaches including changes in the legal system or other social change approaches that focus on gender equality and the engagement of men to reduce violence
[47–49].

Despite the strong study design to assess the efficacy of the HCP delivered intervention on outcomes, limitations and potential problems have been considered. As with other randomized controlled trials, participant drop-out and differential attrition is a concern
[19]. To address potential problems, we have added an exclusionary criterion that women do not plan on relocating within the study period. At the time of enrollment, we also verify contact information for the woman and obtain information for three additional contacts that would know how to get in touch with her. In the analysis plan, we will assess for differential attrition and potentially adjust final models for variables that may have statistically differed between treatment arms. Other approaches may also be used to handle missing data, including multiple imputation, which has been used in other studies examining IPV screening effectiveness
[15].

In addition, staff at referral community agencies that are aware of and engaged with the study may also turnover, which may have a bearing on the quality of service provision. As noted in literature regarding health sector responses to IPV, linkages to community agencies may be a critical component of success

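### Woman-level significance tests on baseline demographics are used to judge clinic randomization and to trigger adjusted models; the covariates should be fixed in advance instead

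*Protocol article*

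**What the plan says.** All of this is in the protocol article. Under *Quantitative assessments & analytic plan*, the first analysis step asks whether the randomization of clinics worked, by "examining if there are statistically significant differences between women’s demographics, by treatment arm, through chi-square or t-tests". Clustering enters only at the fourth step, where the multilevel outcome models will "account for potential clustering for repeat measures, time, and at the clinic level". The section then sets the adjustment rule: "We will subsequently estimate adjusted models if any demographics significantly varied at baseline". The third step compares baseline IPV and the secondary outcomes by arm, but the adjustment rule does not mention them.

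The *Discussion*, on attrition, comes close to the same idea: the team will "potentially adjust final models for variables that may have statistically differed between treatment arms".

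Under *Randomization, sample size, and power analysis*: "Approximately 900 women from 42 health clinics were calculated to be sufficient sample size", clinics were stratified by city zone, and "A conservative intraclass correlation of 0.07 was assumed for clustering at the clinic level". Under *Study population, recruitment, and retention* (text after Figure 1): "Given that clinics were randomized and not individuals, research assistants were not blinded to whether they were in a treatment or control clinic".

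**The concern.** Three things are wrong with using these tests in this way.

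1. **Unit.** The allocation was made on 42 clinics. A plain chi-square or t-test on women treats about 900 women as independent. If women in the same clinic resemble each other, the test rejects too often even when the randomization was sound.
2. **Trigger.** Whether a covariate belongs in the outcome model depends on how well it predicts the outcome. A significant difference between arms does not measure that. The rule also looks only at demographics, so it does not bring in city zone, by which the clinics were stratified, or baseline IPV, a natural prognostic variable here.
3. **Inference.** Women were recruited in the randomized clinics by unblinded research assistants. *Process evaluation* places on-site nurse training before the baseline launch, which indicates that allocation came first. A difference between the women in the two arms may therefore reflect who was recruited, and is not a test of how clinics were allocated.

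At stake are what the report says about randomization, whether an adjusted analysis exists and why, and some precision.

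**Working it through.** **Inputs from the article:** 900 women, 42 clinics, nominal α of 0.05. The 45% attrition allowance does not touch baseline tests. The 900 cannot be uniquely reproduced, because the control rate and sidedness are not stated; it is used here only for the mean clinic size.

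**Assumptions:** equal clinic sizes; 21 clinics per arm in the simulations (the allocation ratio is not stated); ICC of a demographic from 0.01 to 0.07. The article gives no such ICC, so 0.07 serves only as the upper end of the range.

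**Step 1. Clinic size and design effect.** m = 900/42 = 21.4. DEFF = 1 + (m − 1) × ICC. At ICC 0.07: 1 + 20.4 × 0.07 = 2.43.

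**Step 2. True error of an unclustered 5% test.** α* = 2 × P(Z > 1.96/√DEFF). At ICC 0.07: 2 × P(Z > 1.257) = 0.209.

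**Step 3. At least one false signal over eight independent variables.** 1 − (1 − α*)⁸. The number eight and the independence are assumptions; the article does not count its demographics.

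| ICC of demographic | DEFF | True error per test | Simulated (t / chi-square) | At least one of eight |
|---|---|---|---|---|
| 0.01 | 1.20 | 7.4% | 7.7% / 7.1% | 46% |
| 0.02 | 1.41 | 9.9% | 10.2% / 9.2% | 56% |
| 0.05 | 2.02 | 16.8% | 15.7% / 16.9% | 77% |
| 0.07 | 2.43 | 20.9% | 21.1% / 21.4% | 85% |
| valid 5% test | n/a | 5% | n/a | 34% |

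The simulations used 8,000 runs per ICC. In the same runs a t-test on clinic means rejected in 4.4% to 5.4%, so a clinic-level test restores the nominal rate.

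**Step 4. Would valid tests be enough?** No. 1 − 0.95⁸ = 0.34, and for ten variables 1 − 0.95¹⁰ = 0.40. A correctly sized test would still switch adjustment on by chance in a third or more of sound trials.

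**Step 5. Does the rule damage the treatment-effect test?** The rule was simulated with 42 clinics of 21 women, a continuous outcome with ICC 0.07, eight demographics (four prognostic, coefficients 0, 0.15 or 0.3), unclustered t-tests choosing the covariates, a clinic-level random effect in the outcome model, and 1,500 runs per scenario. Adjustment was triggered in 52% to 57% of runs at demographic ICC 0.02 and 83% to 85% at 0.07. Type I error for the treatment effect was 3.5% to 5.5% under the rule, 4.3% to 5.6% never adjusting and 4.6% to 5.9% always adjusting. There was no inflation, and some conservatism where the covariates were strongly prognostic. This does not model recruitment bias.

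**The case against.** The strongest reply is that these error rates belong to a baseline table, not to the trial's conclusion. The outcome models account for clinics, the first analysis is by intention to treat, and adjusted models follow as an addition. This stands, and Step 5 agrees with it. A reader might infer that the treatment-effect test is inflated, or that chance imbalances replace the main model. The article supports neither: it does not say that an adjusted model displaces the unadjusted one, and the *Discussion* wording is tentative and concerns attrition.

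A reader might also infer that prognostic variables without a significant difference are shut out. The analytic plan says when adjusted models are estimated, not exactly which variables enter them, so this goes further than the text.

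The ICC of 0.07 was chosen, as a conservative value, for the sample size. It does not show that demographics cluster that strongly, so 21% and 85% are the upper end of an assumed range.

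It can be said that a condensed article leaves the covariate list and clustered test variants to a fuller document. That is fair for details not stated. Here, however, the article states both the tests and the trigger. That the tests ignore clinics is an inference, from the tests named and from clustering being mentioned only for the outcome models.

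Finally, because recruitment was unblinded, comparing the arms at baseline has a real purpose. That supports showing the comparison. It does not support reading a p-value as a verdict on randomization.

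**Conclusion.** The point holds as a should-fix. The stated check rejects too often under sound randomization: about 7% to 21% per variable instead of 5%, for an assumed demographic ICC of 0.01 to 0.07. The direction holds for any positive ICC; the size rests on that assumption and on about 21 women per clinic. The trigger remains unsound with valid tests (34% over eight independent variables), and as worded it does not bring in city zone or baseline IPV. The consequences are a possibly misleading statement about randomization, an adjusted analysis whose existence depends on chance, and lost precision. Invalid inference on the treatment effect is not shown.

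**What to change.** - Remove significance both as the test of randomization and as the trigger for adjustment, in the analytic plan and in the matching sentence of the *Discussion*.
- Report baseline characteristics by arm descriptively, for example as standardized differences. If tests are kept, make them clinic-adjusted and attach no decision to them.
- Before endline, name city zone, baseline IPV severity and a few prognostic demographics as covariates in the main multilevel model, whatever the baseline comparison shows. Eligibility requires past-year IPV, so the covariate has to be severity, not presence. If the model already treats the baseline value as one of the repeated measurements, do not enter it a second time.

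**Cost.** A few sentences of wording and a few extra model terms, to be kept few with 42 clinics; five zones would use four. City zone is known, and baseline IPV is already to be compared by arm. *Trial status* reports the baseline and three-month surveys complete but not the fifteen-month survey, so on the article's own account the choice can still precede the endline data. A table by arm of women approached, screened positive, eligible and consenting would help to look for recruitment bias, but the fix does not depend on it.
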